**2. Background**

This clinical evaluation was planned following the findings of a genome-wide analysis on narcolepsy, expression analysis of *CPT1B*, and measurement of plasma levels of acylcarnitine discussed below. The Department of Human Genetics of the University of Tokyo and others conducted genome-wide analysis of 500,000 single nucleotide polymorphisms (SNPs) to identify genetic factors related to narcolepsy. SNP rs5770917, located near the *CPT1B* gene on chromosome 22 (22q13.33), was found to be closely associated with narcolepsy. This analysis, conducted with the genomes of Japanese individuals, revealed the risk of narcolepsy to be 1.8-fold higher in those with the risk allele in SNP rs5770917, as compared to those without. SNP rs5770917 has also been associated with narcolepsy in South Koreans. Subsequently we conducted an analysis to determine whether SNP rs5770917 functionally affects mRNA level of *CPT1B* expression and found that people with the risk allele express less *CPT1B* than those without it.

Carnitine palmitoyltransferase 1b (CPT1B) is a rate-limiting enzyme involved in beta oxidation, which is the primary oxidation pathway of fatty acids. CPT1B is responsible for combining carnitine with acyl-CoA produced from fatty acids and producing acylcarnitine. Fatty acids, in the form of acylcarnitine, pass through the inner membrane of mitochondria to enter the matrix. Beta oxidation and the carnitine system have previously been reported to contribute to sleep regulation. Thus the decreased expression of *CPT1B* attributable to the above SNP rs5770917 may impact fatty acid metabolism and sleep regulation. Acylcarnitine levels in the plasma of narcolepsy patients and healthy individuals were measured and compared to determine whether narcolepsy patients may have abnormal fatty acid metabolism. Significantly more narcolepsy patients had abnormally low levels of acylcarnitine. This finding convinced us that L-carnitine, which normalizes acylcarnitine levels and promotes fatty acid metabolism, could have therapeutic value in narcolepsy.

L-carnitine is found in the body and contributes to fatty acid catabolism. L-carnitine was originally used to promote the production of energy from fatty acids in the 1980s in Western countries, and now the compound is widely used in foods or as dietary supplements and functional foods. After evaluating the safety and other aspects of L-carnitine, the Japanese Ministry of Health, Labour and Welfare approved the use of the compound in food under the Food Sanitation Law in 2002. Transient mild diarrhea has been reported at doses of 15 g, but this is attributable to changes in osmotic pressure in the intestine. No substantial adverse reactions are anticipated in this clinical evaluation.

L-carnitine thus has the potential to be a highly safe and clinically beneficial treatment. The clinical evaluation described in this protocol will be conducted as a double-blind, crossover study to verify the efficacy of 510 mg of L-carnitine in narcolepsy patients and thereby generate evidence substantiating this treatment in narcolepsy patients.

**3. Objective and Endpoints**

**Objective**

The objective is to verify the efficacy of 8 weeks of treatment with 510 mg of L-carnitine in narcolepsy patients based on sleep logs, Epworth sleepiness scale (ESS) scores, questionnaire scores including subscales of the Medical Outcomes Study 36-Item Short-Form Health Survey (SF-36) (for subjectively evaluating symptoms and overall health (physical condition)), actigraphy and BMI.

**Endpoints**

Comparison of sleep logs, ESS scores, questionnaire scores (for subjectively evaluating symptoms and overall health (physical condition)), actigraphy, BMI and blood chemistry test data (including plasma carnitine levels) determined following treatment with 510 mg of L-carnitine versus placebo (see 5.5 Endpoints for details).

**4. Subjects**

**4.1 Subject Population**

Patients having narcolepsy with cataplexy (hereafter, “narcolepsy”)

**4.2 Inclusion Criteria**

Narcolepsy patients satisfying all of the following criteria will be enrolled:

• Male or female at least 15 years of age (at time of informed consent)

• Outpatient

• Has personally given written informed consent

**4.3 Exclusion Criteria**

Patients to whom any of the following criteria applies will not be enrolled:

• History of epileptic seizures

• Currently uses acenocoumarol (an anticoagulant)

• Has hypersensitivity to L-carnitine or any placebo ingredient

• Is or may be pregnant, is breastfeeding, or wishes to become pregnant during the clinical evaluation

• Is participating in another clinical study

• Is found by an investigator to be ineligible as a subject

**4.4 Target Sample Size**

Target sample size: A full analysis set of 30.

*Definition of full analysis set:*

The full analysis set is the population consisting of all assigned subjects except for those who do not receive L-carnitine or placebo at all

**5. Methods**

**5.1 Design**

Double-blind, crossover study

510 mg of L-carnitine

Informed consent

Placebo

510 mg of L-carnitine

Placebo

Visit 1　　　　　Visit2　　　　　　Visit3　　　　　Visit4　　　　　　Visit5

Week 0 Week 4 Week 8 Week 12 Week 16

Treatment with L-carnitine or placebo

**5.2 Schedule**

|  | Step 1: 8 weeks  (L-carnitine or placebo) | | |  | Step 2: 8 weeks  (L-carnitine or placebo) | | |
| --- | --- | --- | --- | --- | --- | --- | --- |
|  | Visit1 | Visit2 | Visit3 | | | Visit4 | Visit5 |
|  | Week 0 | Week 4 | Week 8 | | | Week 12 | Week 16 or on discontinuation |
|  |  | Visit 1 + 4 weeks ± 14 days | Visit 2 + 4 weeks ± 14 days | | | Visit 3 + 4 weeks ± 14 days | Visit 4 + 4 weeks ± 14 days |
| Informed consent | ○ |  |  | | |  |  |
| Symptoms and signs | ○ | ○ | ○ | | | ○ | ○ |
| Physical examination | ○ | △ | ○ | | | △ | ○ |
| ESS and other  questionnaires | ○ |  | ○ | | |  | ○ |
| Laboratory tests  (blood sampling) |  | △ | ○ | | | △ | ○ |
| Adverse event  assessment |  |  |  | | |  |  |
| Actigraphy |  |  |  | | |  |  |
| Sleep logs |  |  |  | | |  |  |

○: Mandatory, △: Perform if deemed necessary; Physical tests: Determine blood pressure, pulse rate, height, weight, and body mass index (BMI)

Height need be measured only once during the clinical evaluation. Height determined at another time may be used.

Duration of L-carnitine and placebo treatment will not exceed 11 weeks.

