**5.5 Endpoints**

Sleep logs: Total time for dozing off during the daytime (primary endpoint), the number of naps during the daytime, the number of sleepiness episodes during the daytime, the number of cataplexy attacks, and the number of sleep paralysis episodes in the subjects receiving L-carnitine will be compared against those in subjects receiving placebo. Data obtained during the first 2 weeks (including the first day of treatment) will be excluded because of potential carry-over effect. Nonetheless subjects will be asked to keep their sleep logs during this period.

ESS and questionnaire: The ESS scores and subject-completed questionnaires (including SF-36 subscales) will be obtained on the final day of L-carnitine or placebo treatment period and be compared.

Actigraphy: The activity levels of the subjects will be measured with an actigraph and the activity levels of L-carnitine and placebo treatment periods will be compared. Activity levels will be measured from 11:59 p.m. on the 4th day of Visits 2 and 4 (e.g., Tuesday of the following week if the visit is on Friday) to 7:00 a.m. on the 16th day of the visit (e.g., Sunday of the week after the next if the visit is on Friday).

BMI changes in subjects receiving placebo will be compared against those receiving L-carnitine. Similarly, blood chemistry test data (total cholesterol, triglycerides, and carnitine fraction) of subjects receiving placebo will be compared against the data of subjects receiving L-carnitine.

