**6.5 Dispensing Procedures**

One plastic bottle will be used in each step, and the bottle for a given step will be handed to the subject on the first day of the treatment period. Each bottle contains 231 capsules (which is enough for 11 weeks). Following treatment, each subject will return the remaining L-carnitine or placebo together with the plastic bottle. The dates of dispensing and return of the bottle will be entered in the capsule dispensing chart.

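### Visit windows in Protocol 5.2 are chained, so Visit 3 or 5 can fall before the actigraphy fixed in 5.5 ends, and a step can be much shorter than 8 weeks (minor)

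*Protocol*

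**What the plan says.** - **Visit timing (Protocol 5.2).** Both steps are headed 8 weeks. Each visit is set relative to the preceding visit with the same tolerance, as in "Visit 2 + 4 weeks ± 14 days". Visits 3 and 5 are not tied to the start of their step.
- **Limit on length (5.2, 6.5).** The only explicit limit is an upper one: "Duration of L-carnitine and placebo treatment will not exceed 11 weeks". Supply agrees with it: "Each bottle contains 231 capsules (which is enough for 11 weeks").
- **Intended exposure (section 3, Objective).** The aim concerns "8 weeks of treatment with 510 mg of L-carnitine".
- **Actigraphy (5.5).** Recording starts late on the 4th day after Visits 2 and 4 and continues "to 7:00 a.m. on the 16th day of the visit". The example given for the end is "Sunday of the week after the next if the visit is on Friday".
- **Sleep logs (5.5).** For the primary endpoint, "Data obtained during the first 2 weeks (including the first day of treatment) will be excluded because of potential carry-over effect".
- **Change of treatment (5.1, 5.2, 6.5).** The design and schedule show no gap at Visit 3, and "the bottle for a given step will be handed to the subject on the first day of the treatment period".

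**The concern.** Because each window starts from the actual date of the previous visit, an early Visit 2 brings Visit 3 forward, and an early Visit 3 then shortens the step again. This has two consequences.

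1. **Actigraphy, the firmer one.** 5.5 fixes the recording by days after Visit 2 or 4 and takes no account of when the next visit falls. 5.2 allows that next visit before the recording is over. In Step 1 the subject then receives the second bottle while the first period's recording is still running. In Step 2 treatment ends before the recording does. What is at stake is a clean comparison of activity between the two treatment periods.

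2. **Step length, the lesser one.** A step can comply with 5.2 and still be well short of 8 weeks. Fewer sleep-log days then remain once the first two weeks are dropped, and the assessments at the end of the step follow a shorter exposure than the objective describes.

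**Working it through.** **Inputs.** Interval 28 ± 14 days (5.2); cap of 11 weeks (5.2); 231 capsules (6.5) at 3 per day (6.2); actigraphy from 11:59 p.m. on day 4 to 7:00 a.m. on day 16 (5.5); first 14 log days excluded (5.5); 30 subjects (4.4), so 60 steps.

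**The plan's own figures.** Nominal step: 28 + 28 = 56 days = 8 weeks. Supply: 231 / 3 = 77 days = 11 weeks. Both reproduce.

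**Permitted range.** Each interval is 14 to 42 days. The shortest step is 14 + 14 = 28 days. The longest is 42 + 42 = 84 days from the windows alone, cut to 77 by the cap.

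**Counting the actigraphy days.** In the protocol's example, Friday to the following Tuesday is +4 days, and Friday to Sunday of the week after next is +16 days. The visit day is therefore day 0 and recording ends on visit + 16. The earliest next visit is visit + 14, so days 14 and 15 both come before the end.

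**Hours affected.** From midnight at the start of day 5 to midnight at the start of day 16 is 11 × 24 = 264 h. Adding 7 h gives 271 h. For a visit at noon (assumed):
- day 14: 12 + 24 + 7 = 43 h, and 43 / 271 = 15.9%;
- day 15: 12 + 7 = 19 h, and 19 / 271 = 7.0%.

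**How often.** The protocol gives no distribution of visit dates, so three are assumed for each interval: uniform over 14 to 42 days (pessimistic), triangular around 28 (weight 15 − |d − 28|), and normal with SD 5 days truncated to the window. The two intervals in a step are taken as independent whole days, 29 × 29 = 841 combinations.

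| Event | Uniform | Triangular | SD 5 days |
|---|---|---|---|
| Second interval 14 or 15 days (actigraphy overrun) | 58/841 = 6.9% | 1.3% | 0.4% |
| Of 60 steps | about 4 | 0.8 | 0.3 |
| Step under 42 days | 105/841 = 12.5% | 4.7% | 1.8% |
| Of 60 steps | about 7 | about 3 | about 1 |
| Step of 35 days or less | 36/841 = 4.3% | 0.7% | 0.1% |
| Step of exactly 28 days | 1/841 = 0.12% | 0.002% | about 0 |

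**Sleep-log precision.** Usable days = step − 14: 42 for a 56-day step, 28 for a 42-day step, 14 for a 28-day step. With independent days, the day-sampling variance relative to a 42-day log is 42 / (step − 14). Its mean, with steps capped at 77 days, is 1.10 (uniform), 1.05 (triangular) and 1.03 (SD 5), an increase of 10%, 5% and 3%.

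For one subject with 14 log days on one treatment and 42 on the other, the variance of the difference relative to nominal is (1/14 + 1/42) / (2/42) = 2.0. If half of the nominal variance does not come from day-to-day sampling, 2/42 is added above and below and the ratio is 1.5.

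**The case against.** The strongest reply is that 5.2 has a clear target. Steps are headed 8 weeks, visits carry week labels, and each is due 4 weeks after the last. A tolerance absorbs outpatient slippage and does not redefine the regimen. This stands for step length, and it is why that part is the lesser one.

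On actigraphy there are four replies.
- *5.5 compares the activity of the two treatment periods, so later hours could be read as outside the comparison and trimmed under an analysis plan.* This is fair, but trimming does not recover the lost hours, and 5.5 as written defines the recording through to day 16.
- *The protocol itself allows for carry-over lasting two weeks, so the first hours after the switch may still reflect the earlier treatment.* This weakens the worry about contamination in Step 1 but does not reconcile the two sections.
- *The actigraphy row of the schedule table is blank in the text available, so a drawn bar may have been lost.* That is possible. The wording of 5.5 is explicit on its own, however, and nothing else in the protocol rules out a visit on day 14 or 15.
- *Outside the uniform assumption, fewer than one step in 60 is affected.* This is correct.

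A reader might also infer more than the text supports:
- **That no minimum step length exists.** The windows imply one, 28 days; it is simply low.
- **That subjects would receive half the exposure and one third of the log days.** This needs both visits on their earliest permitted day, at most 0.12% of steps under the assumptions above.
- **That the primary endpoint is biased.** Nothing in the protocol links early visits to treatment; the effect is on precision only.
- **That 84 days from the windows contradicts the 77-day cap.** The cap most naturally governs, so this is a matter of wording.

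**Conclusion.** The concern holds in a limited form, and it is minor.

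The firm part is that 5.2 permits Visit 3 or 5 on day 14 or 15 after Visit 2 or 4, while 5.5 keeps actigraphy running to day 16. That conflict rests only on the protocol's dates and its own weekday example, on the reading that Step 2 treatment begins at Visit 3. Its expected size is 0.4% to 6.9% of steps, and at most 43 of 271 hours of a recording for a noon visit. These figures depend on the assumed visit spread and visit time. Actigraphy is not the primary endpoint.

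The lesser part is that chained tolerances allow steps far below 8 weeks, with only the upper end explicitly capped. Steps under 42 days are about 2% to 12.5% under the same assumptions, and the average day-sampling variance of the sleep logs rises by 3% to 10%. That is one component of the total variance, so the effect on the primary comparison is small.

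**What to change.** Add to 5.2: *Visits 3 and 5 take place at least 16 days after Visits 2 and 4 respectively, after the actigraphy recording has ended.* A visit on day 16 itself is acceptable because recording stops at 7:00 a.m. that morning.

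Preferably also anchor Visits 3 and 5 to the start of their step with a stated minimum, for example day 42. That is 8 weeks less the protocol's own 14 days applied once, and it leaves at least 42 − 14 = 28 log days. Day 42 is a reasonable choice, not the only one. The 11-week cap stays as it is; a clause saying that it overrides the visit windows would remove any doubt.

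**Feasibility.** A permitted Visit 3 date exists for every permitted Visit 2 date. Visit 3 must lie between max(42, Visit 2 + 16) and min(77, Visit 2 + 42). Visit 2 on day 14 allows day 42 to 56, and Visit 2 on day 42 allows day 58 to 77.

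**Cost.** No extra visits, capsules or data, but slightly less scheduling flexibility. The 16-day rule alone would move a visit in 6.9% / 1.3% / 0.4% of steps (uniform / triangular / SD 5). With the 42-day minimum added, the uniform figure is (105 + 58 − 27) / 841 = 136/841 = 16.2%, where 27 combinations break both rules. Counting steps beyond the existing 77-day cap as well (28/841), it is 164/841 = 19.5%, against 5.9% (triangular) and 2.1% (SD 5).

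### Chained ±14-day windows allow the end-of-step visit on day 84, but the treatment cap and capsule supply end on day 77: a minor conflict to reconcile

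*Protocol*

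**What the plan says.** Section 5.2 sets each visit relative to the preceding one: Visit 2 at "Visit 1 + 4 weeks ± 14 days", Visit 3 at "Visit 2 + 4 weeks ± 14 days", Visit 4 at "Visit 3 + 4 weeks ± 14 days" and Visit 5 at "Visit 4 + 4 weeks ± 14 days". A note under the same table reads: "Duration of L-carnitine and placebo treatment will not exceed 11 weeks".

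Section 6.2 gives 3 capsules per day. Section 6.5 says "One plastic bottle will be used in each step", handed out on the first day of the treatment period, and "Each bottle contains 231 capsules (which is enough for 11 weeks". No resupply within a step is described.

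The schedule table puts the ESS and other questionnaires at Visits 1, 3 and 5. Section 5.5 says that the scores to be compared "will be obtained on the final day of L-carnitine or placebo treatment period". Laboratory tests (5.6) are tied to Visits 3 and 5, and weight and BMI (5.7) to Visits 1, 3 and 5; neither is tied to the last treatment day. For the sleep logs, which carry the primary endpoint, 5.5 excludes the first 2 weeks but states no end to the counted period.

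**The concern.** The visit windows and the treatment limits were evidently set separately, and they disagree at the upper end. A site that follows the visit table can hold the end-of-step visit in window after the subject's product has ended. For the ESS and questionnaires, such a visit satisfies 5.2 but not 5.5. For carnitine fraction, lipids and BMI, nothing in the document prevents a value taken off product from being compared as an end-of-treatment value. Because 5.5 gives the log period a start but no end, log days between the end of product and the visit could also enter the primary comparison; that is an inference from its silence. With a target of 30 subjects (4.4), each contributing one L-carnitine step, a few wrongly labelled values would be worth avoiding.

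**Working it through.** Days are counted as days elapsed from the start of a step (Visit 1 for step 1, Visit 3 for step 2). The 11-week limit is read as applying to each step, because the two steps together are planned at 16 weeks.

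**The plan's own supply figure.** 231 capsules (6.5) ÷ 3 per day (6.2) = 77 days = 11 weeks. This reproduces the statement in 6.5 and equals the cap in 5.2.

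**Latest in-window end-of-step visit.** (28 + 14) + (28 + 14) = 84 days. The planned length is 28 + 28 = 56 days and the shortest is 14 + 14 = 28 days.

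**Gap.** 84 − 77 = 7 days at most. At full intake, 84 days would need 84 × 3 = 252 capsules, 21 more than the bottle holds.

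**When a gap arises.** 77 − 56 = 21, so the two visits must together be more than 21 days late.

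| Middle visit of the step (Visit 2 or 4) | Latest in-window end-of-step visit | Days past day 77 |
|---|---|---|
| day 28 | day 70 | 0 |
| day 35 | day 77 | 0 |
| day 36 | day 78 | 1 |
| day 42 | day 84 | 7 |

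**How often.** The documents give no distribution of visit timing, so two assumptions are shown. In both, the two deviations are independent and uniform over whole days.
- Deviations from −14 to +14 days: 29 × 29 = 841 day pairs, of which 28 sum to more than 21. 28/841 = 3.3% of steps.
- Deviations from 0 to +14 days: 15 × 15 = 225 pairs, with the same 28 exceeding 21. 28/225 = 12.4% of steps.

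Each subject has one L-carnitine step, so the expected number of affected L-carnitine steps is 30 × 0.033 = 1.0 or 30 × 0.124 = 3.7.

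**How long.** Among the 28 pairs, gaps of 1, 2, 3, 4, 5, 6 and 7 days occur 7, 6, 5, 4, 3, 2 and 1 times. The mean gap is (7 + 12 + 15 + 16 + 15 + 12 + 7)/28 = 84/28 = 3 days.

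**Effect on log days.** Take the 2-week exclusion as applying to each step. A step with gap g then has 77 + g − 14 = 63 + g counted log days, of which g are off product.
- Extreme: 7/70 = 10%, for a single day pair (both visits exactly 14 days late).
- Sum of g/(63 + g) over the 28 pairs: 7/64 + 12/65 + 15/66 + 16/67 + 15/68 + 12/69 + 7/70 = 1.255.
- Mean in affected steps: 1.255/28 = 4.5%.
- Mean over all steps: 1.255/841 = 0.15% or 1.255/225 = 0.56%.

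**The case against.** The strongest reply is that the cap is printed under the visit table and the two are meant to be read together. No washout is scheduled, so Visit 3 ends one step and begins the next. If 5.5 puts the questionnaires on the last treatment day, then the period ends at the visit and the cap implicitly bounds that visit at 11 weeks. On this reading the cap, the supply and 5.5 agree, and only the far corner of two stacked windows is out of line. That much is fair: every visit up to day 77 satisfies all the sections. But the cap limits treatment and says nothing about visits, and no sentence makes it shorten a window. A site working from the table would regard day 84 as compliant, so the text still needs reconciling.

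A second reply is that missed capsules stretch the bottle. It would last 84 days at 231/252 = 92% intake. That removes the supply limit for such a subject but not the 11-week cap.

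A reader might also infer that the contrast is materially diluted, with a tenth of the log days off product and plasma carnitine most affected. The documents do not support this. The 10% is one extreme pair of dates. A gap in a placebo step removes no active product, so counting subjects with a gap in either step overstates the harm. Section 5.5 itself anticipates carry-over long enough to justify dropping 2 weeks of logs, which exceeds any gap of 1 to 7 days. No section gives carnitine kinetics, so how far levels would fall in the gap cannot be stated.

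**Conclusion.** The inconsistency is real and follows from the protocol's own figures: in-window end-of-step visits extend to day 84, while the cap and the supply both end at day 77. A visit on days 78 to 84 is 1 to 7 days off product, and for the ESS and questionnaires it conflicts with 5.5. The reach is limited to about 1 to 4 L-carnitine steps among 30 subjects, with a mean gap of 3 days where one occurs. Even if the effect vanished at the last capsule, under 1% of the log days behind the primary endpoint would be affected on average. These frequencies rest on assumed uniform and independent visit timing. The 7-day maximum rests only on stated figures. Severity is minor: the text is wrong as written and nearly free to correct, but it does not threaten the trial's conclusion.

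**What to change.** Reconcile 5.2, 5.5, 6.2 and 6.5 so that the latest in-window end-of-step visit, the cap on treatment, the capsule supply and the last-treatment-day assessment agree. Which figure changes is for the sponsor to decide.

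Add to 5.5 that, where a visit falls after product has ended because of the cap or the supply, the log days in that gap are not counted in that step's primary comparison, and the end-of-step values are identified as off product. Confine this rule to that situation. Extended to all log days after the last capsule, it would also remove the logs of subjects who stop capsules early, for example because of an adverse event, and could alter the primary comparison more than the gap does.

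The cost is a line under the schedule table and a sentence or two in 5.5, with matching edits to 6.2 or 6.5 if those figures are the ones changed. Depending on that choice, a few late visits may become out of window.
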